In step 2, patients will follow early exercise-based cardiac rehabilitation performed following all prescription parameters (FITT-VP) and safety criteria recommended by ACSM, 2018 (33). The institutional protocol (**Appendix B**) will be performed with a **frequency** of 2 sessions per day, during the entire hospitalization, with an average of 8 to 10 total sessions; Low **intensity** for aerobic training with METs estimated by the subjective perception of effort of BORG between 9 to 12 reaching between 2 to 3 METs and for resistance training with 2 to 3 series of 60% of the maximum repetitions reached in the 30s sit-to-stand test; **Type** of exercises involved will be aerobic training using the cycle ergometer associated with resistance training using the body's own weight with functional sit-to-stand training; Aerobic training **time** ranging from 3 to 20 minutes. The **Volume or Dose** of aerobic training will be measured by calculating the training dose per session and the total dose applied during hospitalization, providing a value in time x intensity (METs) x frequency of accumulated sessions and total number of sessions x time. The structured **progression** in the protocol focuses on the time of aerobic exercise and the number of series of resistance training. The exercise sessions will follow the protocol presented, however, present individualized prescriptions based on tolerance time during aerobic training with a cycle ergometer and resistance training from the maximum number of repetitions reached in the 30s TSL evaluated

individually before randomization.

Before hospital discharge, patients in the intervention group will receive an exercise guidance booklet (Appendix C) to perform step 3 of semi-supervised and continued cardiac rehabilitation with the exercise time reached at the end of in-hospital rehabilitation, frequency of 5 x per week and progression of 5 minutes each week within the first month after hospital discharge, according to tolerance and self-monitoring of intensity through perceived exertion using the Borg scale, maintained between 9 to 12, to ensure light exercise to moderate intensity. In this phase, patients in the intervention group will be monitored weekly by telephone and will receive a diary (Appendix C) to record the time of daily and weekly activity that they must deliver when investigating when they return for reassessment 30 days after hospital discharge.

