## **RISKS AND BENEFITS**

The risks that the patients involved in the research may present are those inherent to physical activity such as dyspnea, dizziness, fatigue, exhaustion, hypotension, muscle strains, or joint pain. However, the risks will be minimized through the following measures: the proposed exercise will occur within the safety criteria established by the American College of Sports Medicine; For cases of more serious intercurrents such as atrial and ventricular arrhythmias, cardiac decompensation or even cardiorespiratory arrest, the sector has material for cardiorespiratory resuscitation, as well as training of all professionals from the ICU and cardiology ward to manage possible intercurrents.

Regarding the semi-supervised phase, patients will only perform low-intensity exercises with which they will already be adapted during hospitalization, in addition to the large evaluation filter to which they will be submitted to be chosen through the risk stratification of the American Association of Cardiovascular and Pulmonary Rehabilitation (AACPR) (50). Finally, only low-risk patients will be eligible and will undergo semi-supervised follow-up after hospital discharge as recommended by the latest 2020 Brazilian Cardiovascular Rehabilitation Guideline (54).

Among the benefits of this research for the participants, we will have the availability of information about the disease, evaluation, and professional advice on functional capacity and cardiorespiratory fitness, with the supply of an individualized functional exercise prescription booklet after the CPET at the end of the study (Appendix F) with instructions regarding the performance and dose of the exercise, which will lead to a greater stimulus to efficient self-care, enabling better control of your disease, reducing the risk of hospital admissions and morbidity and mortality.

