## APPENDIX B – CARDIAC REHABILITATION PROTOCOL BASED ON IN-HOSPITAL EXERCISE.

### Early CR Protocol – Step 1

| STEPS    | Clinical Assessment                                                                                                                | Type of exercise                                                                                                                                                      | Time                  | Intensity          | Dose      |
|----------|------------------------------------------------------------------------------------------------------------------------------------|-----------------------------------------------------------------------------------------------------------------------------------------------------------------------|-----------------------|--------------------|-----------|
| 0 | KILIP IV/III OU
TIMI 0-1                                                                                                        | Passive sitting in bed                                                                                                                                                | 2 hours               | ---                | ---       |
| 1 | Absence of signs and symptoms of cardiac ischemia > 8 hours (ECG, ischemic markers, or precordial pain) or cardiac decompensation. | Aerobic: lower limb cycle ergometer in bed.

Upper and lower muscle endurance. (Shoulder flexion and abduction, quadriceps block, and triple flexion).          | 3-5 min

1 x 10 | Borg 9-10 (2 METs) | 10MET-min |
| 2 | Absence or low dose of inotropes, vasodilators, and intravenous antiplatelet administration.                                       | Aerobic: lower limb cycle ergometer on the armchair.

Upper and lower muscle endurance. (Shoulder flexion and abduction, quadriceps block, and triple flexion). | 6-10 min

x 10  | Borg 9-10 (2 METs) | 20MET-min |
| 3 | Maintenance of the clinical picture and conditions specified above.                                                                | Aerobic: lower limb cycle ergometer in armchair + walking (10 meters).
Muscular endurance: 30-second chair-stand test.                                             | 9-15 min              | Borg 9-10 (2 METs) | 30MET-min |

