| STEP
S | Type of
exercise | Frequency | Time         | Intensity                  | Dose                   | Weekly diary                                 |
|-----------|---------------------|-----------|--------------|----------------------------|------------------------|----------------------------------------------|
| 1         | Aerobic:
Walking | 5 x week  | 20-
25min | Borg 11-
12
(3 METs) | 300
MET.min-
sem | F:____
T:_____
BORG:____
Dose:_____ |
| 2         | Aerobic:
Walking | 5 x week  | 25-
30min | Borg 11-
12
(3 METs) | 375
MET.min-
sem | F:____
T:_____
BORG:____
Dose:_____ |
| 3         | Aerobic:
Walking | 5 x week  | 30-
35min | Borg 11-
12
(3 METs) | 450
MET.min-
sem | F:____
T:_____
BORG:____
Dose:_____ |
| 4         | Aerobic:
Walking | 5 x week  | 35-
40min | Borg 11-
12
(3 METs) | 525
MET.min-
sem | F:____
T:_____
BORG:____
Dose:_____ |

Subtitle: In step 3, the STEPS are equivalent to the training week.

---

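### The protocol text and Appendix C prescribe different home-phase start times and Borg ranges, so a patient discharged below 20 minutes has two prescriptions

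*Protocol*

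**What the plan says.** Step 3 of the program is the semi-supervised month at home. The protocol describes it in three places.

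- **Early cardiac rehabilitation program.** Home exercise begins "with the exercise time reached at the end of in-hospital rehabilitation, frequency of 5 x per week and progression of 5 minutes each week", with progression subject to tolerance. Borg is "maintained between 9 to 12, to ensure light exercise to moderate intensity". The same section gives in-hospital aerobic time as "ranging from 3 to 20 minutes" and links "BORG between 9 to 12 reaching between 2 to 3 METs". It names Appendix C as both the booklet and the diary that the patient receives.
- **Appendix C.** One schedule is printed for everyone. The note under it reads "In step 3, the STEPS are equivalent to the training week", so its four rows are weeks 1 to 4. Week 1 is 20-25 minutes, five times a week, at Borg 11-12 (3 METs), for 300 MET-min. Weeks 2 to 4 add 5 minutes each, for 375, 450 and 525 MET-min, at the same Borg range. Each row has blank fields for the frequency, time, Borg and dose achieved.
- **Risks and Benefits.** In the home phase "patients will only perform low-intensity exercises with which they will already be adapted during hospitalization".

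Appendix B supplies the time a patient can have reached by discharge: 9-15 minutes in STEPS 5-6 and 12-20 minutes in STEPS 7-8. It counts Borg 9-10 as 2 METs and Borg 11-12 as 3 METs.

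**The concern.** Frequency and weekly progression agree between the text and Appendix C. Start time and Borg range do not. The text's rule is individual and capped by what the patient managed in hospital. The table is fixed, and its lowest week-1 time equals the longest in-hospital time. A patient discharged below 20 minutes therefore has one start time under the text and a longer one in the form taken home.

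The home month carries most of the planned exercise dose before the 30-day reassessment, when the CPET is compared between groups. Appendix B aims for 300 MET-min by hospital discharge, and Appendix C plans 1,650 at home. With 12 patients per group, an intervention specified in two ways makes the delivered dose harder to describe and to relate to outcome, and describing that dose is the general aim stated at the end of the introduction. It also leaves open what patients are told to do when no one is watching the session.

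**Working it through.** **Inputs.** The dose formula is in the section on analysis of aerobic exercise dose: METs × minutes per session × sessions per week. Both sources give five sessions a week. METs follow Appendix B. The time each patient will reach in hospital is not given, so Appendix B's printed limits serve as an assumed range.

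**Reproducing Appendix C.** At the lower time limit of each row:

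- Week 1: 3 × 20 × 5 = 300
- Week 2: 3 × 25 × 5 = 375
- Week 3: 3 × 30 × 5 = 450
- Week 4: 3 × 35 × 5 = 525

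All four stated doses are matched. The total is 1,650, which is 1,650 / (1,650 + 300) = 85% of the planned in-hospital and home dose together.

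**The text's rule.** Week-1 dose = time reached × METs × 5. The four-week total adds 5 minutes each week: 5 × METs × (4 × start + 30).

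| Time reached (min) | METs | Week 1 (MET-min) | 300 / week 1 | Four weeks | 1,650 / four weeks |
|---|---|---|---|---|---|
| 20 | 3 | 300 | 1.0 | 1,650 | 1.0 |
| 15 | 3 | 225 | 1.33 | 1,350 | 1.22 |
| 12 | 3 | 180 | 1.67 | 1,170 | 1.41 |
| 20 | 2 | 200 | 1.5 | 1,100 | 1.5 |
| 15 | 2 | 150 | 2.0 | 900 | 1.83 |
| 12 | 2 | 120 | 2.5 | 780 | 2.12 |

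These rows cover a patient who finishes STEPS 7-8. The first row is the only one that agrees with the table.

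**Outside that range.** The ratio to the tabled 300 exceeds 3 only if the week-1 dose is under 100 MET-min. That means under 100 / (2 × 5) = 10 minutes at 2 METs, or under 100 / (3 × 5) = 6.7 minutes at 3 METs. An example is a patient who stops at the 9-minute lower limit of STEPS 5-6 and trains at home at Borg 9-10: 9 × 2 × 5 = 90, and 300 / 90 = 3.33.

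**Risk section.** A patient discharged at 12 or 15 minutes would start at 20-25 minutes under Appendix C, longer than any session that patient reached in hospital. A patient discharged at 20 minutes is also taken past it at the upper end of the row.

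**The case against.** The best defence is that Appendix C describes the planned course. The text expects 8 to 10 sessions on average and Appendix B has eight active STEPS, so the average patient can reach STEP 8. Its stated dose of 60 MET-min equals 20 minutes at 3 METs, and starting there gives exactly 300, 375, 450 and 525. The section on dose analysis also speaks of a standardized goal with individual tolerance limits and weekly monitoring, and the blank diary fields let the delivered dose be computed from what was done.

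Much of this stands. The table fits a patient who completes STEP 8 at its upper time limit, and recorded values limit the harm to the dose data. But STEP 8 itself allows 12 to 20 minutes, so completing it does not imply leaving at 20. The tolerance wording permits adjustment without saying which start time is prescribed.

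The Borg conflict runs one way. Borg 11-12 lies inside 9-12, so a patient following Appendix C satisfies the text, while one following the text at Borg 9-10 departs from Appendix C. The different labels, light to moderate in one place and low intensity in another, change no number, and the text itself calls Borg 9-12 low intensity for step 2.

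Two stronger readings are tempting. A reader might infer that doses typically differ more than threefold. They do not: against the stated 300 that needs under 10 minutes at Borg 9-10. For a patient who finished STEPS 7-8, the ratio passes 3 only at 12 minutes and 2 METs against 25 minutes at 3 METs (375 / 120 = 3.13), and Appendix C does not state 375 as its week-1 dose. A reader might also infer that adherence is judged against the table, because the diary fields share its rows. No section defines adherence or makes that comparison.

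**Conclusion.** The contradiction holds and should be corrected, at moderate size. For a patient finishing STEPS 7-8, the tabled week-1 dose is 1.0 to 1.67 times the text's dose at 3 METs and 1.5 to 2.5 times at 2 METs. Over four weeks the ranges are 1.0 to 1.41 and 1.5 to 2.12. The sources coincide only at 20 minutes and 3 METs.

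These figures assume Appendix B's conversion from Borg to METs, five sessions a week, the full 5-minute weekly increase, and discharge times within Appendix B's limits for STEPS 7-8. The distribution of discharge times is unknown, so the number of patients affected cannot be stated. The existence of two start rules depends on none of these assumptions.

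**What to change.** Reconcile the step 3 paragraph of the program section, Appendix C and the home-phase paragraph of Risks and Benefits so that one start-time rule and one Borg range apply to every patient, including one who leaves hospital below 20 minutes. Which start time and which range are right is for the investigators to settle and is not judged here. Then compute each patient's weekly target dose from the reconciled prescription, and state which end of a time range enters the dose: Appendix C uses the lower limit, whereas Appendix B uses the upper (STEP 8: 20 × 3 = 60).

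The cost is wording in the protocol and the diary form. No extra data, visits or patients are needed.

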### Cardiohemodinamic safety of early cardiac rehabilitation

The safety of the institutional protocol tested in this trial will occur through notifications

of adverse events during and after the CR sessions provided to patients in the intervention group. We will report adverse events session by session, listing the main ones: arrhythmias, chest pain, borg>13, drop in systolic blood pressure (SBP) above 10 mmHg, and cardiorespiratory arrest. Other events not previously listed will also be recorded in the patient follow-up and evaluation form as per Appendix A.

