**Session 7:** Session start: HR:\_\_\_\_\_bpm RF:\_\_\_\_\_bpm SpO2:\_\_\_\_\_ % BP:\_\_\_\_\_mmHg  
End of session: HR:\_\_\_\_\_bpm RF:\_\_\_\_\_bpm SpO2:\_\_\_\_\_ % BP:\_\_\_\_\_mmHg  
Security: ☐ Angina ☐ Arrhythmia \_\_\_\_\_ ☐ Borg>=13 ☐ Fall of SBP >=10mmHg  
☐ CPA ☐ Others:\_\_\_\_\_ Vasoactive drug (Dose) ☐ \_\_\_\_\_ Devices:\_\_\_\_\_  
\_\_CR summary:\_\_\_\_\_

**Session 8:** Session start: HR:\_\_\_\_\_bpm RF:\_\_\_\_\_bpm SpO2:\_\_\_\_\_ % BP:\_\_\_\_\_mmHg  
End of session: HR:\_\_\_\_\_bpm RF:\_\_\_\_\_bpm SpO2:\_\_\_\_\_ % BP:\_\_\_\_\_mmHg  
Security: ☐ Angina ☐ Arrhythmia \_\_\_\_\_ ☐ Borg>=13 ☐ Fall of SBP >=10mmHg  
☐ CPA ☐ Others:\_\_\_\_\_ Vasoactive drug (Dose) ☐ \_\_\_\_\_ Devices:\_\_\_\_\_  
\_\_CR summary:\_\_\_\_\_

**Surplus sessions:** Any adverse events? Which? \_\_\_\_\_

| COMPLEMENTARY EXAMS                                                                                                                                                                                                                                              |                          |
|------------------------------------------------------------------------------------------------------------------------------------------------------------------------------------------------------------------------------------------------------------------|--------------------------|
| Electrocardiogram (1): _____
 Regular rhythm  Atrial fibrillation  Pacemaker  RBBB  LBBB  Others _____ | Date: ____ / ____ / ____ |
| Echocardiogram (1): EF _____ PAP _____ Others: _____                                                                                                                                                                                                      | Date: ____ / ____ / ____ |
| X-RAY (1): _____                                                                                                                                                                                                                                          | Date: ____ / ____ / ____ |

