|          |                                                                     |                                                                                                                                |                                         |                    |           |
|----------|---------------------------------------------------------------------|--------------------------------------------------------------------------------------------------------------------------------|-----------------------------------------|--------------------|-----------|
|          |                                                                     |                                                                                                                                |                                         |                    |           |
| 4 | Maintenance of the clinical picture and conditions specified above. | Aerobic: lower limb cycle ergometer on armchair + walking (75 to 100 meters).

Muscular endurance: sitto stand exercise. | 9-15min

2 x 60% test repetitions | Borg 9-10 (2 METs) | 30MET-min |

Subtitle: The frequency of the STEPS is twice a day following the established order. The progression of the exercises focuses on the exercise time, following the order of the STEPS. The aim of the protocol is to achieve an accumulated 90 MET-min until ICU discharge.

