### **Early CR Protocol – Step 2**

| STEPS | Avaliação Clínica                                            | Tipo de exercício                                                           | Tempo                            | Intensidade  | Dose |
|--------------|---------------------------------------------------------------------|------------------------------------------------------------------------------------|-----------------------------------------|---------------------|-------------|
| 5     | Maintenance of the clinical picture and conditions specified above. | Aerobic: Walking + stair training

Muscular endurance: sitto stand exercise. | 9-15min

2 x 60% test repetitions | Borg 11-12 (3 METs) | 45MET-min   |
| 6     | Maintenance of the clinical picture and conditions specified above. | Aerobic: Walking + stair training

Muscular endurance: sitto stand exercise. | 9-15min

2 x 60% test repetitions | Borg 11-12 (3 METs) | 45MET-min   |

|          |                                                                     |                                                                                    |                                          |                     |           |
|----------|---------------------------------------------------------------------|------------------------------------------------------------------------------------|------------------------------------------|---------------------|-----------|
| 7 | Maintenance of the clinical picture and conditions specified above. | Aerobic: Walking + stair training

Muscular endurance: sitto stand exercise. | 12-20min

3 x 60% test repetitions | Borg 11-12 (3 METs) | 60MET-min |
| 8 | Maintenance of the clinical picture and conditions specified above. | Aerobic: Walking + stair training

Muscular endurance: sitto stand exercise. | 12-20min

3 x 60% test repetitions | Borg 11-12 (3 METs) | 60MET-min |

Subtitle: The frequency of the STEPS is twice a day following the established order. The progression of the exercises focuses on time and intensity variables, following the order of the STEPS. The aim of the protocol is to guarantee 210 MET-min until discharge from the ward and 300 MET-min until hospital discharge, by the sum of the execution dose spent in ICU and ward.

## APPENDIX C - PRESCRIPTION AND FOLLOW-UP FORM FOR EARLY CR Step 3

### Early CR Protocol – Step 3

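### Adverse-event recording is specified only for in-hospital sessions; the semi-supervised home phase, about 20 of 28 to 30 sessions, has no specified event record

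*Protocol*

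**What the plan says.** The secondary objectives include identifying the adverse-event rate and the safety level of the protocol evaluated in the trial. The section on the early cardiac rehabilitation program defines three steps and makes continued rehabilitation at home (step 3) one of them, for the intervention group only.

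On recording, the safety section says "We will report adverse events session by session". It lists arrhythmia, chest pain, Borg above 13, a systolic pressure drop and cardiorespiratory arrest, and sends unlisted events to the Appendix A form. That form prints a block for each of sessions 1 to 8, with vital signs and event tick-boxes. One line for surplus sessions follows, asking "Any adverse events? Which". The program section expects in-hospital rehabilitation "with an average of 8 to 10 total sessions".

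For step 3, the intervention group is followed weekly by telephone and "will receive a diary (Appendix C) to record the time of daily and weekly activity". Each weekly row of the Appendix C table has four spaces: frequency, time, Borg and dose. The budget section mentions the telephone calls but not what is asked in them.

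**The concern.** The objective attaches the event rate to the protocol evaluated, and step 3 belongs to it. Yet no form or procedure in the document says where chest pain, dizziness or a walk stopped early at home would be written down. The program section tells patients to interrupt exercise for such symptoms, but nothing provides for recording that this happened at home.

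Home walks are planned at 20 to 40 minutes, against at most 20 minutes for any in-hospital STEP, and without staff present. If the plan is followed as written, the safety result rests on supervised sessions, and a statement about the safety of the whole programme would have no systematic home data behind it. No analysis plan can repair this later, because it concerns what is collected.

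**Working it through.** **Dose in hospital.** Appendix B gives METs, minutes and dose per STEP. Dose = METs × minutes, using the top of each time range.
- Step 1 (STEPS 1 to 4): 2×5 + 2×10 + 2×15 + 2×15 = 10 + 20 + 30 + 30 = 90. This reproduces the stated target: "The aim of the protocol is to achieve an accumulated 90 MET-min until ICU discharge".
- Step 2 (STEPS 5 to 8): 3×15 + 3×15 + 3×20 + 3×20 = 45 + 45 + 60 + 60 = 210, and 90 + 210 = 300. This reproduces "210 MET-min until discharge from the ward and 300 MET-min until hospital discharge".

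**Dose at home.** Appendix C gives 3 METs, 5 sessions a week and four weekly time ranges. The printed doses use the bottom of each range.
- 3×5×20 = 300; 3×5×25 = 375; 3×5×30 = 450; 3×5×35 = 525. All four match the table.
- Total: 300 + 375 + 450 + 525 = 1650 MET-min.

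**Share of printed dose.** Home: 1650/(300 + 1650) = 1650/1950 = 84.6%. In hospital: 300/1950 = 15.4%.

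Appendix B prints the longest times and Appendix C the shortest, so the in-hospital share is at its highest here. With the shortest in-hospital times (2×(3+6+9+9) + 3×(9+9+12+12) = 54 + 126 = 180) and the longest home times (15×(25+30+35+40) = 1950), it is 180/2130 = 8.5%.

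**Share of sessions.** This is the relevant unit, because events are to be reported by session. Home sessions: 5 × 4 = 20. In-hospital sessions: 8 to 10.

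| Type of record | 8 in hospital | 10 in hospital |
|---|---|---|
| Tick-box block | 8/28 = 28.6% | 8/30 = 26.7% |
| Any event prompt, including the surplus line | 8/28 = 28.6% | 10/30 = 33.3% |
| No specified event record (home) | 20/28 = 71.4% | 20/30 = 66.7% |

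**Surplus sessions.** On the stated average, 8 − 8 = 0 to 10 − 8 = 2 sessions per patient fall on the free-text line.

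**Listed events against the home diary.** Borg has a space, but one per week for five walks, so a single walk above 13 cannot be identified. The other listed events have no space, and neither does an interrupted session.

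**The case against.** The strongest counter-argument is about scope. The safety section speaks of the institutional protocol. The program section ties that term to Appendix B and to the hospital stay, and the abstract refers to the safety of inpatients. On that reading Appendix A prompts for events at every session in scope. The reading is possible, but the objective names the protocol evaluated and step 3 is part of the program, so the document does not settle it. If the rate is in-hospital only, it leaves the objective unanswered for step 3 and should be labelled accordingly.

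Three stronger readings are tempting, and the document does not support them.
- *Event recording stops at session 8.* Only the tick-boxes and printed vital-sign fields stop there. The surplus line accepts an event in a ninth session, although one shared line suits session-by-session reporting poorly.
- *The home phase is unsupervised, so home events cannot be captured.* The protocol calls it semi-supervised, with weekly calls and a reassessment 30 days after discharge. These contacts could collect events; what is missing is any statement that they do. Borg is also partly captured.
- *The event rate will describe about 15% of the programme.* The arithmetic is right, but MET-min is not the denominator of a per-session rate. Nor does the document say that an in-hospital rate will be presented as that of the whole programme.

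**Conclusion.** The gap is real and confined mainly to step 3. About 20 of 28 to 30 planned sessions, or 1650 of 1950 printed MET-min, have no specified adverse-event record, while the safety objective is worded for the protocol as a whole. The session figures assume 8 to 10 in-hospital sessions and full adherence to 5 walks a week for 4 weeks. The dose figures use the printed doses and one session per in-hospital STEP. The free-text line after session 8 is a minor matter of form layout. The change is worth making under either reading of the safety section's scope.

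**What to change.** Add patient-reportable event fields to each week of the Appendix C diary: for example chest pain, dizziness or fainting, a session stopped early and why, and unplanned medical contact. State that the weekly call already planned asks about these and enters them. Say in the safety section whether the adverse-event rate includes step 3. Report per-session rates separately for the supervised in-hospital phase and the home phase, and label any rate without home data as in-hospital only. Repeating the Appendix A session block beyond session 8 is an optional small edit.

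The cost is an edit to the diary, a short call script and slightly longer calls. Home events will be self-reported and unverified, which is a reason not to pool them with supervised events, and the total event count may rise.
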